2003). In addition, gene doping is also a future drug strategy one will have to deal with. Stable transfection of the Epo gene in tissue has already been shown in animal models (Hojman et al., 2007). Gene doping was therefore in 2003 added to WADA and the IOC's list of "Prohibited Substances and Methods in Sport"(Pascual et al., 2004). This stresses the importance of developing new and more sensitive Epo analysis. Thus, future anti-doping tests should not only focus on detecting rHuEpo and its derivatives, but also on biological markers that change by Epo exposure. Such markers have been studied. Total hemoglobin mass and reticulocyte percentage (_OFFhr-score_) and the so-called blood-passport (Gore et al., 2003) have been suggested as markers for Epo abuse. The problem with the OFF_hr-score_ is that the cut-off values are based on the average population level, and because of large inter-individual differences the cut-off values (upper and lower limit) are very broad, in order to avoid false-positive results. This ultimately leads to a low detection level (Lundby & Robach, 2009; Borno et al., 2010). Also the blood pass, where one follows the athletes’ blood values over time, proved not to guarantee a drug free sport (Borno et al., 2010).

Proteomics has proven to be a good way to characterize all proteins expressed in a biological system, such as blood. We have already in a previous study showed that 16 days of treatment with rHuEpo resulted in significant changes in several serum proteins (Christensen et al.

2010). The main objective of this project is to investigate the effect of prolonged rHuEpo treatment on changes in the serum proteome of healthy young men. Furthermore, we want to investigate the effect of rHuEpo and physical activity on these markers, as it is important to elucidate the effect of physical activity, if these markers should be used as anti-doping markers in the future.

Epo receptors are found in a variety of different types of tissues other than the bone marrow, including neurons, astrocytes, microglia, cancer cells, gastric mucosal cells and especially muscle tissue. The effect of Epo in these tissues still needs to be fully elucidated.

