**PURPOSE**

To identify new serum biomarkers to detect abuse of rHuEpo. Secondarily, we want to examine the effects of 10 weeks of rHuEpo treatment and training on a wide range of other parameters e.g. turnover of fat, carbohydrate, and protein, muscle type changes, and activation of satellite cells in skeletal muscle.

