**Methods:**

• Metabolic profile, hyperinsulineamic eugluceamic clamp, muscle and fat biopsies, blood tests, maximum oxygen uptake, DEXA scan

**Primary end-points:** Proteomics analysis of serum

**Secondary end-points:** Substrate metabolism, fiber typing, and activation of satellite cells

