**SUBJECTS**

A total of 40 healthy young men will be included in the present study. These will be recruited through the web page www.forsøgsperson.dk and various notices on educational institutions in Aarhus (see attached notice).

Because the effect of rHuEpo on some of the required parameters have not previously been elucidated, it has not been possible to make a power calculation. However, from similar studies in our laboratory, it is estimated that approximately 10 subjects in each group is enough to reach statistical power. Furthermore, in a previous study on a group of 8 subjects it was possible to detect significant changes in the proteome 16 days after treatment with rHuEpo (Christensen et al., 2010).

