- **MRI scanning:** MRI will be used to measure intrahepatic and intramyocellular lipid content. The liver and the tibialis anterior muscle will be scanned using a technique that combines MR imaging with localized proton MR spectroscopy with a voxel of 3x3x3cm, a 1.5T MR unit will be used together with a breath holding for 17 sec. Before entering the scanning room the subject will be asked about contra induced circumstances in relation to normal procedures for MRI. The subjects will be asked to remove any metal from pockets and remove jewelry. The subjects will be informed that MRI is a safe procedure without any risk of radiation. There will be a loud sound during the scanning, and the subjects will be given earplugs.

 
[figure not shown]

**Serum:** Serum will be collected before the study and on days 8, 15, 21, 36, 50, 64, 71, and 78 and 92 during the wash-out period. Hematological levels will be measured throughout the study, and treatment will be discontinued if the values are abnormal (Hematocrit >55%). The following will be measured; Hemoglobin, erythrocytes, iron, transferrin, ferritin, reticulocytes, haptoglobin, albumin, alkaline phosphatase, bilirubin, LDH, plasma hemoglobin, VLDL, FFA, ghrelin, and cholesterol. Proteomics analysis will be performed on blood samples taken before the study at baseline and on days 21, 71, and 92.

**Blood pressure measurements:** The subjects' blood pressure will be monitored throughout the study on the days when blood will be sampled. This is done to ensure that the treatment does not induce increased blood pressure.

Blood and tissue samples are used for analyses, and thereafter destroyed. A bio bank is therefore not created.

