**STATISTICS**

Group comparisons will be made with standard statistical methods (t-test and ANOVA or equivalent non-parametric tests). Within the groups, a paired t-test or equivalent non-parametric test will be used. A p-value below 0.05 is regarded as a significant result.

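### The only significance rule, p<0.05 with no multiplicity control, also governs the many-protein primary endpoint, so chance markers are expected in proportion to the number of proteins tested

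*Protocol*

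**What the plan says.** The protocol's STATISTICS section sets out the whole inferential plan in three sentences:

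- Between groups: "Group comparisons will be made with standard statistical methods (t-test and ANOVA or equivalent non-parametric tests").
- Within groups: "Within the groups, a paired t-test or equivalent non-parametric test will be used".
- Decision rule: "A p-value below 0.05 is regarded as a significant result".

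The lay description adds only that standard methods will be used.

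The primary end-point is "Proteomics analysis of serum", and the PURPOSE section gives the aim: "To identify new serum biomarkers to detect abuse of rHuEpo". No protein is named in advance. The BACKGROUND section describes the breadth of the technique: "Proteomics has proven to be a good way to characterize all proteins expressed in a biological system, such as blood". The Serum paragraph under METHODS gives the sampling: "Proteomics analysis will be performed on blood samples taken before the study at baseline and on days 21, 71, and 92". DESIGN has four groups of 10 men, rHuEpo or placebo, each with or without training.

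The protocol does not mention multiplicity, a false discovery rate, a familywise error rate or a validation sample. It does not say how many proteins will be quantified.

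**The concern.** A threshold of 0.05 limits the error of one test. The primary endpoint here is a screen in which every quantified protein can be tested. Used as the decision rule for each protein, the threshold passes 5% of the unaffected proteins on each contrast.

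The result of this trial is a list of proteins. If an unknown and possibly large share of that list is there by chance, readers cannot tell which entries deserve follow-up. This matters for the intended use: BACKGROUND itself criticises existing blood markers for the wide limits needed to avoid false positives.

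This goes beyond detail left for an analysis plan. The protocol states a significance criterion and makes no exception for the primary endpoint. An analysis plan that controls error across proteins would have to replace or qualify that criterion for proteomics.

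**Working it through.** The protocol has no power, familywise error or false discovery figure to reproduce. Its one error-rate figure is 0.05, and for a single test of a true null the chance of a false call is indeed 0.05.

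**Inputs.** From the protocol: threshold 0.05 (two-sided assumed), four groups of 10, baseline plus three later proteomics days. Assumed: number of proteins m = 20, 50, 100 or 300.

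**Step 1. One contrast on one day, no true effect.** Expected chance findings = 0.05 × m. Probability of at least one = 1 − 0.95^m.

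| m (assumed) | Expected chance findings | Probability of at least one |
|---|---|---|
| 20 | 1 | 64% |
| 50 | 2.5 | 92% |
| 100 | 5 | 99.4% |
| 300 | 15 | >99.9% |

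The probability column needs independence between proteins. The expected counts do not.

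**Step 2. Several days and groups.** Testing each of three later days against baseline in the two rHuEpo groups gives 6 tests per protein. At m = 50 that is 0.05 × 6 × 50 = 15 false test results if nothing changes; at m = 100 it is 30. These count test results, and one protein can contribute more than one.

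**Step 3. Share of false entries when some proteins do change.** Suppose 10 proteins truly change and each is found with 80% power, giving 8 true finds on average. False calls are 0.05 × (m − 10), and the share is false/(false + 8):

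- m = 50: 2.0/(2.0 + 8) = 20%
- m = 100: 4.5/(4.5 + 8) = 36%
- m = 200: 9.5/(9.5 + 8) = 54%

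**Step 4. Benjamini-Hochberg at 5%.** Simulated two-sample t-tests with independent proteins, m = 200, 10 truly changed. The 20 v 20 rows pool the training and non-training arms.

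| Comparison and true effect | False calls: p<0.05 → BH | True finds of 10: p<0.05 → BH |
|---|---|---|
| 20 v 20, 0.91 SD | 9.5 → 0.2 | 8.1 → 2.6 |
| 20 v 20, 1.325 SD | 9.5 → 0.4 | 9.8 → 8.0 |
| 10 v 10, 1.325 SD | 9.4 → 0.2 | 7.9 → 1.9 |
| 10 v 10, 1.8 SD | 9.4 → 0.4 | 9.7 → 6.4 |

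A repeat run agreed to within about 0.1 in each cell. At 10 v 10 and 1.8 SD, the mean false share of the list falls from 48% to about 5%.

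**The case against.** The best defence is that the STATISTICS section is generic. It never mentions proteomics, and it does not say that p-values are unadjusted or that the rule applies protein by protein. A threshold of 0.05 is also the usual way to state an alpha level and could be applied to adjusted p-values, and an analysis plan not shown here might do so. This stands as a caution on wording: a reader might infer that the protocol expressly orders an unadjusted test of each protein, and it does not. The point survives because the criterion is the only one given, covers the primary endpoint without exception, and would need changing or qualifying.

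A second defence is that this is a discovery study. No anti-doping test or cut-off is to be adopted from it, and the text speaks of possible future use. This also stands. It would go too far to infer that the primary conclusion could not be trusted at all. But the protocol calls the hits significant, does not label them as candidates and plans no confirmation.

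Third, much larger counts can be built. Six pairwise and four within-group tests on each of three days make 30 tests per protein, which gives 0.05 × 30 × m = 75 to 450 for m = 50 to 300. The documents do not support reading this as a number of false markers. The grid is not prescribed: ANOVA could be one omnibus test per day, and several of the comparisons (for instance, changes within the placebo groups) would not support an rHuEpo marker. The figure also counts tests; 75 exceeds the 50 proteins available. In simulation about 55% of unaffected proteins are flagged at least once on that grid, or about 27 to 165 proteins.

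Finally, a reader might turn this into a criticism of the statement that "it is estimated that approximately 10 subjects in each group is enough to reach statistical power". SUBJECTS says openly that no power calculation was possible, so that sentence is not part of this point.

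**Conclusion.** The concern holds in a limited form. The protocol's single criterion, p<0.05 without multiplicity control, governs a many-protein primary screen. With no true effect, one contrast on one day gives about 0.05 × m chance findings: from 1 at m = 20 to 15 at m = 300, with more when several days and groups are tested.

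The size rests on an assumed m, which the protocol does not give. To say that a false positive is almost certain would go beyond the documents: at m = 20 the chance is 64%, and correlation between proteins would generally lower these probabilities, though not the expected counts. The false share of the final list also depends on how many proteins truly change and by how much.

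**What to change.** In the STATISTICS section, give the proteomics endpoint its own rule:

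- Pre-specify one rHuEpo versus placebo contrast, for example baseline-adjusted protein level at day 71. The choice of day and contrast is the sponsor's; several are defensible.
- Across all quantified proteins in that contrast, declare a marker only if it passes Benjamini-Hochberg at a 5% false discovery rate.
- Treat the other days and the training interaction as separate families.
- Report proteins with only nominal p<0.05 as unconfirmed candidates for validation.

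This takes a few lines of text and no new data. The real cost is sensitivity. In the 20 v 20 example with m = 200 and 10 true markers of 0.91 SD, about 2.6 are found instead of 8.1, while false calls fall from about 9.5 to 0.2. At 1.325 SD the loss is smaller (8.0 instead of 9.8). Proteins that miss the threshold stay visible in the nominal list, so leads are kept but labelled for what they are.

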**BACKGROUND**

Erythropoietin (Epo) is produced in the kidneys when the oxygen levels in the blood become too low. Epo stimulates the formation of new red blood cells in the bone marrow. Epo is used as a medicine for kidney and cancer diseases, leading to a lack of red blood cells.

Epo increases red blood cell production and hence the amount of oxygen that can be transported around the body. It is shown that prolonged use of synthetic Epo (rHuEpo) leads to an increase in the period of time a given physical work can be performed, therefore it will continue to be abused by athletes, especially in endurance sports. This happens despite the fact that rHuEpo was added to the anti-doping list already in 1990. It is therefore important to find a robust method to detect this abuse. Not only to ensure fair competition but also to reduce the abuse and the side effects that follow, e.g increased risk of blood clots.

The existing method for measuring the abuse of rHuEpo approved by the World Anti-Doping Agency (WADA) is based on differences in the sugar groups bound to rHuEpo and Epo produced in the body, respectively. Whether this approach will be effective against new synthetic Epo products are still unknown. Future Epo tests should therefore be based on biological markers, that changes when Epo levels rise. Various blood markers related to the amount of red blood cells have already been investigated, but these methods have proven to be very conservative, since the boundaries of the normal range is very wide in order to avoid false-positive results.

Proteomics is a method by which you can look at all the proteins in blood at the same time. Even proteins that have changed very little can be distinguished. The main objective of this project is to investigate the effect of prolonged treatment with rHuEpo on changes in blood proteins in healthy young men. We have in a previous study with 16 days of treatment with rHuEpo shown changes in blood proteins. It is hoped that some of these proteins can be used as marker for Epo abuse in the future. We furthermore want to explore the effect of physical activity on these proteins, since athletes will always be physically active. The effect of physical activity itself is therefore important to elucidate, if these proteins should be used in a future anti-doping test.

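### The flat p<0.05 rule covers a primary end-point that is an open set of serum proteins, so the share of false Epo markers is uncontrolled

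*Protocol*

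**What the plan says.** The only primary end-point, in the list that follows DESIGN, is "Proteomics analysis of serum". No protein, panel or candidate list is named. PURPOSE states a discovery aim: "To identify new serum biomarkers to detect abuse of rHuEpo". BACKGROUND describes the breadth of the method: "Proteomics has proven to be a good way to characterize all proteins expressed in a biological system, such as blood". The lay description says the same: "Proteomics is a method by which you can look at all the proteins in blood at the same time".

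The STATISTICS section gives the tests. Between groups: "Group comparisons will be made with standard statistical methods (t-test and ANOVA or equivalent non-parametric tests"). Within groups: "Within the groups, a paired t-test or equivalent non-parametric test will be used". It closes with the decision rule: "A p-value below 0.05 is regarded as a significant result". The lay STATISTICS section says only that standard methods will be used.

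Under METHODS, the serum paragraph sets the sampling: "Proteomics analysis will be performed on blood samples taken before the study at baseline and on days 21, 71, and 92". DESIGN has four groups of 10 men. No adjustment for multiplicity, false discovery rate or validation step appears anywhere in the protocol, and SUBJECTS says that a power calculation was not possible.

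**The concern.** A 0.05 threshold limits the error of one test of one variable. Here the primary end-point is as many variables as there are quantified proteins. If each is judged at 0.05, unaffected proteins enter the marker list at a rate of 1 in 20 per comparison, and nothing in the protocol limits how much of the list they make up. Naming one deciding day and one Epo-versus-placebo contrast would not cure this, because the multiplicity comes from the proteins.

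The result of the trial is a list of proteins that might later support an anti-doping test. BACKGROUND itself criticises existing blood markers because their limits had to be set wide to avoid false positives. A list with no stated error rate does not tell a reader how many of its entries to believe.

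**Working it through.** The protocol derives no power or overall error rate, so there is no figure of its own to reproduce. The threshold of 0.05 is a declared rule.

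**Inputs from the protocol:** 0.05 per test (two-sided assumed, since sidedness is not stated); 10 men per group; proteomics at baseline and on days 21, 71 and 92.

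**Assumptions, because the protocol gives no figure:** m = 100, 300 or 1000 quantified proteins; 10 of them truly changed by 1 SD; independent proteins; two-sample t-test; one day and one contrast.

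**1. No protein changes.** Expected false markers = 0.05 × m. Chance of at least one = 1 − 0.95^m.
- m = 20: 1 expected; 1 − 0.95^20 = 64%.
- m = 100: 5 expected; 1 − 0.95^100 = 99.4%.

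Correlation leaves the expected number unchanged but lowers the chance of at least one. At m = 100 with common correlation 0.3 it is about 94 to 95%.

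**2. Ten proteins change by 1 SD.** Expected false calls = 0.05 × (m − 10), which is 4.5, 14.5 and 49.5 at m = 100, 300 and 1000. Expected true calls = 10 × power.
- 10 v 10: power 0.562, so 5.62 true calls. Ratios: 4.5/10.12 = 44%, 14.5/20.12 = 72%, 49.5/55.12 = 90%.
- 20 v 20: power 0.869, so 8.69 true calls. Ratios: 4.5/13.19 = 34%, 14.5/23.19 = 63%, 49.5/58.19 = 85%.

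Simulation, which averages the false share itself rather than taking a ratio of averages, gives 43%, 72% and 90% at 10 v 10, and 33%, 62% and 85% at 20 v 20.

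**3. When false markers are the majority.** With π the share of proteins truly changed, false calls outnumber true ones when 0.05(1 − π) > power × π, that is π < 0.05/(0.05 + power).
- Power 80%: 0.05/0.85 = 5.9%.
- 10 v 10, 1 SD: 0.05/0.612 = 8.2%.

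If π = 10% at 80% power, the false share is 0.045/(0.045 + 0.080) = 36%.

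**4. Benjamini-Hochberg at 5%, simulated.** The false share falls to about 5%. True proteins kept, out of 10:

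| Comparison | Effect | m = 100 | m = 300 | m = 1000 |
|---|---|---|---|---|
| 10 v 10 | 1 SD | 0.9 | 0.4 | 0.1 |
| 10 v 10 | 1.5 SD | 4.6 | 2.6 | 1.3 |
| 20 v 20 | 1 SD | 5 | 3 | 2 |

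**5. More comparisons.** Three post-baseline days triple the expected false calls for one contrast. If nothing changes at m = 100, that is 3 × 5 = 15. Four groups, and within-group as well as between-group tests, add further calls.

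**The case against.** Four points can be made for the plan.

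*Multiplicity is often left to the analysis plan, and the sentence does not say that the p-value is unadjusted.* This stands in part: an adjusted p-value below 0.05 would comply with the wording. But the protocol is not silent. It states a general rule, lists ordinary single-variable tests, and reserves no exception for its primary end-point. Followed as written, it leaves the error rate uncontrolled.

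*This is a discovery study.* The lay BACKGROUND only hopes that some proteins will serve as markers. That bears on how strict the control should be, and is a good reason to accept a 10% rate or to keep an exploratory list. It does not justify having no stated rate.

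*Most declared markers need not be false.* Correct. A reader might infer from the larger figures that most will be, or that the trial is practically certain to report spurious markers. The protocol gives neither the number of proteins nor the changed share, and it cites an earlier 16-day study in which several serum proteins changed, so a complete absence of effect is not its expected case. At m = 100 with 10 true changes, the false share is below one half at either group size.

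*The rank-test fallback.* A reader might add that a paired rank test on 10 men cannot go below 2/2^10 = 0.002 and so cannot support claims across the proteome. That does not hold as a criticism of the plan. Non-parametric tests between groups are also allowed, and their floor at 10 v 10 is about 0.00001. The 0.002 floor comes from having 10 pairs, and a paired sign-flip permutation test shares it.

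**Conclusion.** The point holds. The significance rule does not fit the primary end-point: it admits about 5% of unaffected proteins at each comparison and leaves the false share of the marker list uncontrolled. Under the stated assumptions that share is about 43% to 90% at 10 v 10 and 33% to 85% at 20 v 20, for 100 to 1000 proteins. The 20 v 20 figures suppose that the training arms are pooled, which the protocol does not state.

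A false majority is conditional on a small truly changed share, below about 6% at 80% power. Even with 10% of proteins changed at that power, the false share is 36%, far above 5%. The number of proteins, the number changed and the effect size are all assumptions. The expected number of false calls does not depend on independence; the chance of at least one does.

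**What to change.** In STATISTICS, restrict the p<0.05 sentence to single, named variables. For serum proteomics, add a rule along these lines:

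- A protein is a candidate Epo marker only if its Benjamini-Hochberg adjusted p-value for the randomised Epo-versus-placebo comparison is below a stated false discovery rate: 5%, or 10% for a screening list.
- The adjustment runs across all quantified proteins, and across days 21, 71 and 92 unless one deciding day is named.
- The number of proteins tested is reported, and proteins with only unadjusted p<0.05 are labelled exploratory.

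The text should also say whether the comparison is 10 v 10 or pools the training arms.

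This takes a few sentences and no new data. The real cost is sensitivity. At 10 v 10, a 5% rate loses nearly all true 1-SD changes and about half or more of those at 1.5 SD; at 20 v 20, about half to four fifths of the 1-SD changes are lost. The exploratory list should therefore be kept as leads for later study.
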